## Abstract

**Background:**

Almost all of the 820,000 people in the UK with dementia will experience Behavioural and Psychological Symptoms of Dementia (BPSD). However, research has traditionally focused on treating cognitive symptoms, thus neglecting core clinical symptoms that often have a more profound impact on living with dementia. Recent evidence (Kales et al, 2007; Ballard et al, 2009) indicates that the popular approach to managing BPSD - prescription of anti-psychotic medication - can increase mortality and the risk of stroke in people with dementia as well as impair quality of life and accelerate cognitive decline. Consequently, there is a need to evaluate the impact that non-pharmacological interventions have on BPSD; we believe physical exercise is a particularly promising approach.

**Methods/Design:**

We will carry out a pragmatic, randomised, single-blind controlled trial to evaluate the effectiveness of exercise (planned walking) on the behavioural and psychological symptoms of individuals with dementia. We aim to recruit 146 people with dementia and their carers to be randomized into two groups; one will be trained in a structured, tailored walking programme, while the other will continue with treatment as usual. The primary outcome (BPSD) will be assessed with the Neuropsychiatric Inventory (NPI) along with relevant secondary outcomes at baseline, 6 and 12 weeks.

**Discussion:**

Designing this study has been challenging both ethically and methodologically. In particular to design an intervention that is simple, measurable, safe, non-invasive and enjoyable has been testing and has required a lot of thought. Throughout the design, we have attempted to balance methodological rigour with study feasibility. We will discuss the challenges that were faced and overcome in this paper.

**Trial Registration:**

ISRCTN01423159

## Background

"*Country air, moderate exercise, and a tonic regimen may retard the progress of senile dementia and suspend to some extent its termination*[1]". J.E.D. Esquirol, 1845

Dementia is a degenerative disease of the brain that leads to impairment of memory and global intellectual deterioration without affecting consciousness [2]. The prevalence rises sharply with increasing age: 5% of those over 65 and 20% for those aged over 80 will have dementia [3]. Dementia is also associated with a cluster of non-cognitive symptoms and behaviours that are an integral part of the syndrome. Commonly described as Behavioural and Psychological Symptoms of Dementia (BPSD), they include disturbed perception, thought content, mood or behaviour that frequently occur in patients with dementia [4]. Although recognised as core to the phenomenology of dementia in Alzheimer's seminal case studies [5], these symptoms have received relatively little attention from the research community. This is surprising given that upwards of 80% of people with dementia will experience BPSD at some point during the course of their illness [6]. Apart from the obvious distress for the person, BPSD are commonly associated with reduction in the quality of life for the person as well as their caregivers [7]; increase of caregiver stress [8], costs of care [9]; and unsurprisingly premature institutionalization [10].

Although there is some evidence supporting the treatment of BPSD with antipsychotics, there have been increasing concerns over the safety of these drugs for people with dementia. Two recent studies indicate that there is a long-term risk of mortality in patients with dementia who take antipsychotic medication [11,12]. Non pharmacological alternatives that have been reported to have a positive effects include music therapy, bright light therapy, behavioural interventions and exercise[13]. As well as the potential improvement in physical well being exercise has been demonstrated to have a positive effect on cognitive symptoms and mood [14,15]. Interventions such as exercise may offer a safer effective alternative to pharmacological treatments and could also be empowering to individuals with dementia and may reduce carers' burden.

Heyn et al carried out meta-analysis of exercise in dementia and reported data on 30 trials of exercise [16]. The authors reported on trials that included strength, cardiovascular or flexibility regimes; and analysed for functional, cognitive or behavioural outcomes. A significant positive effect of exercise on behavioural outcomes was reported (Effect Size = 0.54; 95% Confidence Interval = 0.36-.72). However these trials do not provide a full picture of the effectiveness of exercise on BPSD for a number of reasons. There was considerable heterogeneity in terms of the interventions, and exercise was often combined with other behavioural interventions. Thus, it is difficult to isolate the impact that exercise has had on behavioural outcomes. Some regimes were quite complex and require a high degree of physical fitness that would preclude many older adults with complex physical problems and moderate or profound dementia from performing them. Moreover, they were potentially unsustainable without the support of trained therapists. Finally, the relatively high cost of delivery and specialist input required may prevent the interventions being used more widely. Most trials included in the analysis were relatively small, with only two of the eight studies that reported effects on behaviours having samples in excess of 100 participants.

We have designed a study that aims to evaluate the effectiveness of exercise as a therapy for behavioural and psychological symptoms of dementia. This will be a pragmatic randomised trial conducted in a community cohort in the UK nested within a larger programme of research. The overarching programme investigates the impact of various psychosocial interventions for people with dementia, those who care for them and professionals that support them (Evidence Based Interventions in Dementia-EVIDEM). This has been a challenging design process, which has seen the project team - supported by an independent steering group - attempt to strike a balance between achieving a feasible and sustainable intervention, which could be widely adopted in the target population while maintaining scientific rigour in its evaluation. In the following, we describe the resultant and final methodology and discuss the benefits & limitations to our approach.

## Study hypothesis

A programme of tailored incremental exercise (through walking) improves the symptoms and outcome of Behavioural and Psychological Symptoms of Dementia

## Methods/Study Design

This trial has been granted ethical approval by the Outer North East London Research Ethics Committee, REC reference number: 09/H0701/67.

We will undertake a pragmatic, randomised, controlled, single-blind, parallel-group trial. Community-dwelling individuals with a diagnosis of dementia or suspected dementia who also have a carer willing and able to be a co-participant in the exercise regime will be recruited to this evaluation.

Participants will be randomly allocated to one of two arms: the treatment arm, which includes receipt of an individually tailored regime of walking (the intervention; exercise therapy-ET) in addition to treatment as usual (TAU) or the control arm which receives treatment as usual only (see Figure 1). Treatment as usual may include home care, attendance at day care facilities, visits by health professionals, receipt of medication, respite care etc.

**Figure 1 F1:**
[figure not shown]
**Randomisation of participants and data collection**.

Both the treatment and control arms will be re-assessed for all outcomes at weeks 6 and 12. Further telephone contact will occur at 26 weeks to assess adverse events, mortality, change in domiciliary status and adherence to exercise regime. The randomisation ratio for the two groups will be 1:1 (ET:TAU). An Independent randomisation officer will use a computer algorithm to perform the randomisation centrally after the initial interview, and will communicate the results to the participants, the GP and to the exercise therapist; but not to those collecting research data.

### Primary Objective

To determine the effectiveness of physical exercise delivered through a programme of incremental walking for treating behavioural and psychological symptoms of dementia (as defined by Neuropsychiatric Inventory scores) compared with treatment as usual (TAU).

### Secondary Objectives

To determine the effect of exercise on 1) the quality of life of people with dementia; 2) psychotropic medication usage; 3) move to a residential care facility; 4) mortality levels; 5) caregivers' perceived level of burden. We will also carry out an economic evaluation of the intervention and qualitatively explore participants' views about the intervention and barriers to treatment.

### Recruitment

The selection criteria for participation in the Evidem-E trial are outlined in Table 1 (Table 1). Participants with a clinical diagnosis of dementia or 'suspected dementia' with at least one significant BPSD symptom defined by the Neuropsychiatric Inventory (NPI)[17] (excluding the domains of delusions and hallucinations) will be eligible for the trial. Diagnosis of dementia will be confirmed in accordance with ICD-10 Diagnostic Criteria for Research (DCR-10). A risk assessment will be performed to assess the suitability of participants for the intervention at baseline. This assessment will include measurement for risk of falls through the Falls Risk Assessment Tool (FRAT) [18] and Timed Unsupported Steady Standing (TUSS) [19].

**Table 1 T1:** Selection criteria for inclusion/exclusion from the Evidem-E trial

*Inclusion criteria*	*Exclusion criteria*
Diagnosis of: a. Dementia in primary or secondary care OR b. Suspected dementia confirmed by the researcher to ensure the DCR-10 criteria are met; Presence of a carer (professional, friend or family member, who does not necessarily have to live with the participant); Presence of BPSD measured through NPI. [NPI score in any one sub-set (except only hallucination or delusion) more than or equal to 2 in severity and more than or equal to 2 in frequency]; Consent of participant, or in the case of an individual who is not capable of giving informed consent, the assent of the participant with agreement of carer; Consent of carer.	Cardio-respiratory condition, neurological or musculo-skeletal condition of a degree that prevents participation to even the modified exercise regime unsafe or not possible. Three or more falls in the previous year ("frequent fallers") assessed by FRAT or high falls risk defined by TUSS; Uncontrolled medical problems, which the GP considers would exclude participants from undertaking the exercise programme; for example, acute systemic illness' such as pneumonia, poorly controlled angina, acute rheumatoid arthritis, unstable or acute heart failure; Sensory impairment to an extent that prevents dyad facilitated exercise; Participant or carer dissent to engage in the exercise programme.

Individuals with dementia known to the General Practitioner or secondary care will be identified and suspected new cases will be assessed to confirm diagnosis. Regular reminders about the study will be sent to participating practices and secondary care teams within the network catchment's area. A central register of all referrals will be maintained.

There are four potential sources of recruitment:

• The locally adopted Dementia Registry (DemReg) of people with dementia interested in participating in research.

• GP practices that are affiliated to the EVIDEM Research Group

• Memory assessment services and community mental health services (e.g. Admiral Nurses) recruited via CNWL NHS Foundation Trust

• Self referral

### Interventions

Physical exercise will be delivered as an individually tailored regime of walking designed to become progressively intensive and last between 20-30 minutes. This will be facilitated by a qualified exercise therapist and delivered to participants in the treatment arm of the trial (Figure 2) in the area around their own home. The exercise therapist will facilitate physical exercise in the participant-carer dyad with the expectation that the dyad will perform the exercise regime regularly and independently of the therapist at least 5 times per week. The intervention has been structured so that the therapist adopts a phased withdrawal approach utilising both face-to-face contacts and telephone support contacts.

**Figure 2 F2:**
[figure not shown]
**Intervention schedule**.

The dyad on the intervention group will also be asked to complete a visual analogue scale called the Rating of Perceived Exertion (RPE) [20]. Perceived exertion is based on the physical sensations a person experiences during physical activity, including increased heart rate, increased respiration or breathing rate, increased sweating, and muscle fatigue. Although this is a subjective measure, a person's exertion rating may provide a fairly good estimate of the actual heart rate during physical activity (Borg, 1998). The exercise therapist will not only assess the RPE but train participants to evaluate themselves and will encourage the dyad to extend walking exercise to 60-70% of RPE.

The participants in the treatment arm will be asked to record their daily activities and RPE throughout the 12 weeks of their participation using a diary designed to meet the specification of this study.

### Outcome Assessments

Assessments will be conducted according to Figure 1. Participants will be visited in either their own homes, or a mutually acceptable convenient location (e.g. GP's clinic), by a trained research worker (RW) masked to arm allocation.

The primary outcome measure will be changes to behavioural and psychological symptoms measured by the Neuropsychiatric Inventory (NPI) at baseline as well as 6 and 12 weeks of participation.

Secondary outcome measures will be changes to: participants' mental health (GHQ)[21], participants' quality of life (DemQOL-Proxy)[22], and caregivers' burden of caring (short ZBI) [23]. The secondary outcomes will also be measured at baseline, 6 and 12 weeks into the trial.

Participants' level of physical activity and compliance with the intervention will be measured through daily diaries, Rate of Perceived Exertion (RPE), blood pressure and heart rate monitoring. Diaries will also provide qualitative information in regards to participants' views about the intervention.

We will also carry out an Economic Evaluation through the Client Service Receipt Inventory [24], which will be administered at baseline and 12 weeks into the trial.

Domicile and mortality change will be measured at follow-up, 26 weeks into the trial via a structured telephone interview.

The exercise programme will be initiated and supervised by the Exercise Therapist. Baseline and subsequent evaluations will be undertaken by RW. An independent researcher (IR) will collect the primary outcome data (NPI) at weeks 6 and 12, which will be completed by telephone with the aim of minimising the risk of un-blinding group allocation to research workers.

### Sample size

Based on anticipated between-group absolute risk difference of 30% in number of people with BPSD symptoms measured by the NPI, a sample size of 146 participants will give 90% power to detect this difference with 95% confidence. This calculation includes a 20% attrition estimate. The sample size calculations have been described in Table 2.

**Table 2 T2:** Power calculations

Control	Intervention	Difference	N (including compensation for 20% attrition)
0.8	0.4	0.4	70 (88)
0.8	0.5	0.3	116 (145)
0.8	0.6	0.2	238 (298)

(calculated by http://www.stat.ubc.ca/~rollin/stats/ssize/b2.html)

### Statistical Methods

Baseline demographic and outcome data will be compared between the two randomisation groups. Categorical data will be analysed using the chi-square test. Continuous data will be analysed using the t-test or if the data is found to be non-normally distributed, we will use the Wilcoxon Rank-Sum test.

Outcomes at 6 and 12 weeks will be compared between randomisation groups using analysis of co-variance (ANCOVA) for continuous data. The relevant baseline scores will be included as the co-variate in order to adjust for any potential baseline differences in the respective outcome. Categorical outcomes will be compared using the chi-square test.

All data will be analysed on an intention-to-treat basis, where appropriate imputation of missing data will be implemented. Under the assumption that data are missing at random multiple imputation will be used.

All analyses will be completed using the statistics package STATA.

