Careful consideration was taken in regards to blinding the researcher to the allocation status of the participants. The single blind design leaves us vulnerable to unmasking group allocation during the interaction between researcher and participant during visits. This everyday conversation is essential to building a rapport with participants and ensuring they feel comfortable in participating. All study personnel including researchers and therapists will repeatedly remind participants of the importance of not disclosing their group allocation. However, the risk will remain, and so we decided to include a second 'independent' researcher whom would collect our primary outcome data (NPI) at 6 and 12 weeks. The premise for this approach is that this researcher can take a less 'personal' tone and thus minimize the risk of conversation with the dyad that might un-blind group allocation. However, there remains a risk that the dyad will divulge information about the group they have been allocated to. Therefore the efficacy of blinding will be assessed at each time point, by personnel collecting data who will record which arm they believe each dyad is randomised to.

Separating the effect of psychosocial contact (from the exercise therapist) from the exercise intervention has proved to be the biggest challenge in our study. We decided to address this problem by introducing two periods during the intervention: 1-6 weeks whereby the participants in the intervention group will be trained and supported by an exercise therapist and 6-12 weeks when participants will receive absolutely no contact with the therapist. This stage will also help to assess the intervention's feasibility and sustainability in a community population. The symptoms of BPSD tend to be relatively stable over short time periods (i.e. months) so the two windows provided by this method should detect responses influenced purely because of exercise and not by any residual benefits of interaction with the therapist. Although we have tried to control for contacts between participants and the exercise therapist, we could not control for the social contact between the person with dementia and their carer. Dyadic walking may encourage not just physical activity but psychosocial support from the carer as well.

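### The per-visit ANCOVAs do not estimate how the arm effect changes between the supported and no-contact windows, and the design cannot attribute the week-12 effect purely to exercise

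*Protocol article*

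**What the plan says.** The Discussion treats separating therapist contact from exercise as the hardest design problem of the study. Its answer is two periods: "1-6 weeks whereby the participants in the intervention group will be trained and supported by an exercise therapist", then "6-12 weeks when participants will receive absolutely no contact with the therapist". It gives the second period a further, modest role: "This stage will also help to assess the intervention's feasibility and sustainability in a community population". From the stability of symptoms ("The symptoms of BPSD tend to be relatively stable over short time periods (i.e. months") it concludes that "the two windows provided by this method should detect responses influenced purely because of exercise", and not any residual benefit of contact with the therapist.

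Statistical Methods fixes the analysis: "Outcomes at 6 and 12 weeks will be compared between randomisation groups using analysis of co-variance (ANCOVA) for continuous data". On adjustment it says: "The relevant baseline scores will be included as the co-variate in order to adjust for any potential baseline differences in the respective outcome". It states no arm-by-visit term and no contrast between weeks 6 and 12. Neither the primary nor the secondary objectives include a comparison of the two periods. The only comparator is treatment as usual.

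**The concern.** The Discussion gives the two windows an inferential job that the stated analysis does not do. Each ANCOVA estimates the difference between arms at one visit, measured from a pre-randomisation baseline. The week-12 estimate is therefore cumulative over both windows, and nothing in the plan estimates what happened to the arm effect after contact stopped.

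Two things are at stake. First, if the week-6 and week-12 results differ in significance, a reader has only two p-values from which to judge whether benefit was lost or gained once the therapist withdrew, and two p-values do not test that. Second, a positive week-12 result could be reported as an effect of exercise alone, although every participant in the exercise arm also received therapist contact in weeks 1 to 6.

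**Working it through.** **Inputs from the document.** 1:1 allocation; 90% power; 95% confidence, taken as two-sided alpha 0.05; proportions 0.8 and 0.5; 20% attrition; assessments at baseline, 6 and 12 weeks; baseline score as covariate.

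**Assumptions.** The article gives no NPI standard deviation and no correlation between visits. Effects are therefore in SD units, the same correlation r is assumed between all three assessments, with r = 0.3, 0.5 and 0.7, and normal theory is used.

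**1. The plan's own figure, which supplies the number of completers.** The uncorrected size per arm is [1.960 × √(2 × 0.65 × 0.35) + 1.282 × √(0.8 × 0.2 + 0.5 × 0.5)]² / 0.3² = 51.0. With the continuity correction it is (51.0/4) × [1 + √(1 + 4/(51.0 × 0.3))]² = 57.5, so 58 per arm and 116 in total. Then 116/0.8 = 145, or 146 as an even number. Table 2 is reproduced. It concerns a binary outcome, so it says nothing about precision for a comparison of windows. It is used here only for n = 58 per arm.

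**2. Precision of one visit and of the contrast.**
- Single-visit ANCOVA: SE = √[(2/n)(1 − r²)].
- Week-12 minus week-6 arm effect: SE = √[(2/n) × 2(1 − r)].
- Correlation of the two adjusted estimates: (r − r²)/(1 − r²) = r/(1 + r).
- Ratio of contrast SE to single-visit SE: √[2/(1 + r)].

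| r | SE, one visit | Correlation of estimates | SE, contrast | Ratio | 95% CI half-width |
|---|---|---|---|---|---|
| 0.3 | 0.177 | 0.23 | 0.220 | 1.24 | 0.43 |
| 0.5 | 0.161 | 0.33 | 0.186 | 1.15 | 0.36 |
| 0.7 | 0.133 | 0.41 | 0.144 | 1.08 | 0.28 |

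Power of the contrast to detect complete loss of a 0.5 SD week-6 effect is 62%, 77% and 94%. For a 0.3 SD effect it is 28%, 37% and 55%.

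**3. What two p-values would show.** With an identical 0.5 SD effect at both visits, power per visit is 81%, 87% and 96%. Drawing the two test statistics from a bivariate normal with the correlations above, exactly one visit is significant in 27%, 18% and 6% of trials. Week 6 alone is significant in 14%, 9% and 3%. In all of these trials the true effect has not changed.

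**4. What the week-12 ANCOVA and the contrast each do** (4,000 simulated trials per scenario, r = 0.5).

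| Arm effect at week 6, week 12 (SD) | Week-12 ANCOVA rejects | Contrast rejects | Mean contrast |
|---|---|---|---|
| 0.5, 0 (gone) | 4.9% | 76% | −0.50 |
| 0.5, 0.25 (half lost) | 34% | 26% | −0.25 |
| 0.5, 0.5 (unchanged) | 86% | 4.9% | 0.00 |

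The week-12 ANCOVA holds its 5% level when nothing is left, and its mean estimate is 0.496 when 0.5 SD remains. It answers whether benefit is present at week 12. The contrast answers how much the arm effect changed.

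**5. Attribution.** Suppose the effect is due to exercise alone and continues: 0.5 SD at both visits, contrast 0. Suppose instead that it is due to contact alone and carries over fully: again 0.5 SD at both visits, contrast 0. The data are the same in both cases, so neither the ANCOVAs nor the contrast can tell them apart. Symptom stability over months does not help. If symptoms move slowly, a gain made through contact by week 6 is more likely to be still there at week 12.

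**The case against.** The case on the other side is substantial.

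- **The week-12 ANCOVA is sound.** It is a randomised, baseline-adjusted, intention-to-treat comparison after six weeks without the therapist. This stands in full. A reader might infer that the plan has no valid analysis of whether benefit outlasts therapist contact. The documents do not support that: step 4 shows the week-12 test has the right error rate and answers exactly whether exercise therapy is better than usual treatment at that point.
- **The article never concludes that benefit will persist.** It says only that the no-contact stage will help to assess sustainability. Its strong sentence is about attribution. This stands, and the criticism belongs on that sentence.
- **No objective compares the windows, and the article does not propose judging change from two p-values.** Both are true. The rates in step 3 therefore measure a misreading that the plan leaves open, not one that it commits.
- **An arm-by-visit term is ordinary analysis-plan detail.** Its absence from a condensed article would not by itself be a finding. What remains is that the article states a property of the two windows which neither its stated analysis nor its design delivers.
- **The contrast would not cure the attribution problem and would be imprecise.** Both are true. A reader might expect it to be more precise than a single-visit effect because the visits are correlated. After baseline adjustment with equal correlations it is less precise. It would be more precise only if weeks 6 and 12 were sufficiently more correlated with each other than with baseline, on which the article is silent.

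**Conclusion.** The point holds in a limited form. The article claims that its two windows will detect responses due purely to exercise. The planned ANCOVAs give no estimate of the change in arm effect between the windows. Without an attention control, the week-12 effect includes any carry-over from contact in weeks 1 to 6, and no re-analysis of these data would remove it. The planned comparison of arms at week 12 is unaffected.

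On size: if the two p-values were used to judge change, a constant 0.5 SD effect would give discordant results in 6% to 27% of trials. A direct contrast would have a 95% CI half-width of about 0.28 to 0.43 SD. Both ranges rest on 58 completers per arm and equal between-visit correlations of 0.3 to 0.7, which are assumptions. It does not follow that the ANCOVAs must be replaced as the main analysis.

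**What to change.** 1. **Statistical Methods.** Keep the week-6 and week-12 ANCOVAs. Add, as a pre-specified secondary analysis, the week-12 minus week-6 difference in arm effect with its 95% CI, taken from the arm-by-visit term of one baseline-adjusted repeated-measures model. State that any comment on change between the windows rests on this contrast and not on the two p-values.
2. **Discussion.** Reword the sentence on the two windows. The no-contact window shows whether benefit is present, and how far it is maintained, after therapist contact ends. It cannot attribute the effect purely to exercise, because contact effects may carry over and there is no attention control.

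The cost is wording and one further model on data already to be collected, in the same software. The downside is imprecision: the contrast's SE is about 1.08 to 1.24 times that of a single-visit effect on the assumptions above. An interval that includes zero must therefore not be reported as proof that the effect was maintained.

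### Categorical outcomes get an unadjusted chi-square test while continuous ones are baseline-adjusted; the test is valid, but less efficient and gives no risk difference

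*Protocol article*

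**What the plan says.** In the protocol article, Statistical Methods plans ANCOVA for continuous outcomes at 6 and 12 weeks, with the matching baseline score as covariate. For binary and other categorical outcomes it says only: "Categorical outcomes will be compared using the chi-square test". No covariate, effect measure or interval is named for them. The same section plans an intention-to-treat analysis with imputation where appropriate: "Under the assumption that data are missing at random multiple imputation will be used".

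The Sample size section is framed in a binary outcome: "Based on anticipated between-group absolute risk difference of 30% in number of people with BPSD symptoms measured by the NPI". It states that "a sample size of 146 participants will give 90% power to detect this difference with 95% confidence", and adds: "This calculation includes a 20% attrition estimate". The row of Table 2 that matches the target has 0.8 in the control arm and 0.5 in the intervention arm.

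The Primary Objective and Outcome Assessments sections define the primary outcome through NPI scores and changes in them, measured at baseline, 6 and 12 weeks. No sentence says that the NPI will be dichotomised for analysis.

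**The concern.** The plan treats its two types of outcome differently and gives no reason. Its argument for ANCOVA, to deal with chance baseline differences, applies equally to a binary NPI outcome. The Discussion also describes BPSD as fairly stable over months, so the baseline NPI score should be prognostic at 6 and 12 weeks.

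The sentence matters because of the sample size. If the proportion with BPSD is analysed, nothing else in the article says how. Two things are then at stake: some power, and a direct estimate with an interval of the 30-point difference on which the trial is sized. A chi-square test by itself yields only a p-value.

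**Working it through.** **Inputs from the article.** Proportions 0.8 and 0.5, two arms at 1:1, 90% power, 95% confidence and 20% attrition. The confidence level is read as a two-sided 5% test, which is the version that reproduces Table 2.

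**Step 1: reproduce the stated sample size.** With mean proportion 0.65 and difference 0.3:

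- n = [1.960 × √(2 × 0.65 × 0.35) + 1.282 × √(0.8 × 0.2 + 0.5 × 0.5)]² / 0.3² = [1.322 + 0.821]² / 0.09 ≈ 51.0 per arm.
- With continuity correction: (51.0 / 4) × [1 + √(1 + 4 / (51.0 × 0.3))]² ≈ 57.5, so 58 per arm and 116 in total.
- With attrition: 116 / 0.8 = 145, or 146 for equal arms.

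This matches the article. The same formula gives the other two rows, 70 (88) and 238 (298).

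**Step 2: power of the planned test at the design rates.** For the uncorrected chi-square with 58 per arm, z = (0.3 × √58 − 1.322) / 0.640 = (2.285 − 1.322) / 0.640 ≈ 1.50, so power is about 93%.

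**Step 3: what adjustment adds.** The documents give no correlation between baseline NPI score and later status, so it is assumed over a range. In the simulation, a latent normal outcome is correlated r with the baseline score and cut so that 80% of controls have BPSD, with 58 per arm and 2,000 trials per setting. The rates 0.8 v 0.5 correspond to a latent shift of 0.84 SD. The smaller effect is a shift of 0.54 SD, which takes 0.8 to Φ(0.842 − 0.54) ≈ 0.62. The value 0.54 equals the behavioural effect size from the meta-analysis cited in Background. Using it as a latent shift is an assumption.

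| Assumed r | 0.8 v 0.5: chi-square / adjusted | 0.8 v 0.62: chi-square / adjusted |
|---|---|---|
| 0.3 | 94% / 96% | 60% / 61% |
| 0.5 | 93% / 96% | 58% / 66% |
| 0.6 | 94% / 98% | 58% / 67% |

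The simulation standard error is about 1 point near 60% (√(0.6 × 0.4 / 2000) = 0.011). Allowing for repeat runs, adjusted power is about 94-98% in the first scenario and 61-69% in the second. With no treatment effect, type I error was near 5% for both methods (4.1-5.4% in one set of runs).

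**Step 4: what the estimate would look like.** At 0.8 v 0.5 with 58 per arm, the unadjusted risk difference has standard error √((0.16 + 0.25) / 58) = 0.084. Its 95% interval is 0.30 ± 1.96 × 0.084, about 0.14 to 0.46. The named test does not supply this.

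**Step 5: which baseline value to use.** Table 1 admits only people with BPSD on the NPI. If the outcome uses the entry definition, binary baseline status is the same for everyone and cannot be a covariate. The continuous NPI score can.

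**The case against.** The strongest reply is that nothing here is wrong. An unadjusted comparison of randomised groups is valid, and the chi-square alone exceeds the stated 90% power at the design rates. Naming a test does not prevent a risk difference from being reported, and an article may leave that to the full analysis plan. All of this stands. What remains is that the sentence states the method rather than staying silent, so a later plan would have to replace it.

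A reader might also infer more than the documents support:

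- **That the chi-square cannot be combined with multiple imputation.** It can. Chi-square statistics can be pooled by the D2 rule. In a simulation with 73 per arm, 20% missing and 20 imputations, this gave type I error 5.2% and power 93.4%. A risk difference pooled by Rubin's rules gave 5.7% and 93.6%. The two plans do not conflict, although D2 still returns only a p-value.
- **That the test is unsuitable for rare 26-week events.** The article says "Domicile and mortality change will be measured at follow-up, 26 weeks into the trial" but gives no event rates. Over assumed rates of 1-15%, the exact size of the uncorrected chi-square never exceeds 5.2%, and it is conservative at very low rates. Fisher's exact test is more conservative still: 1.0% against 4.6% at a 5% rate with 58 per arm.
- **That the primary analysis is certainly this chi-square.** The primary outcome is worded as change in NPI, which ANCOVA would cover. The article does not reconcile that wording with its binary sample size. That is a separate matter.

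**Conclusion.** The point holds as a matter of efficiency and of estimation, not of validity. If the proportion with BPSD is analysed, the stated test makes no use of the baseline NPI score and does not directly produce the quantity in which the trial is sized. At the design rates the loss is a few points of power, from about 94-98% down to about 93%. At the smaller assumed effect it runs from almost nothing at r = 0.3 to roughly 10 points at r = 0.6. The figures near 60% belong to that smaller effect and do not show that the trial is underpowered at its own design.

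The sizes rest on three assumptions: baseline correlations of 0.3 to 0.6, a latent normal outcome, and 58 analysed per arm.

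**What to change.** Replace the chi-square sentence, for binary NPI outcomes, with: 'Binary NPI outcomes at 6 and 12 weeks will be analysed by logistic regression with randomised arm and the continuous baseline NPI score as covariates (binary baseline status is constant by the entry criterion). Results will be reported as a marginal risk difference with 95% confidence interval, pooled over imputations by Rubin's rules.'

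The cost is a change of wording. The baseline score is already collected, the sample size does not change, and standard software can fit the model. The handling of the 26-week events need not change on this account.
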